# Effectiveness of a mHealth platform-based lifestyle integrated multicomponent exercise (*PF-Life*) program to reverse pre-frailty in community-dwelling older adults: a randomized controlled trial study protocol

**DOI:** 10.3389/fpubh.2024.1389297

**Published:** 2024-06-07

**Keywords:** pre-frailty, mHealth platform, lifestyle-integrated exercise, older adults, protocol

## Abstract

**Background:**

Pre-frailty represents an ideal window of opportunity to potentially prevent frailty and disability. Early and effective interventions to delay or reverse pre-frailty are public health imperative. The present trial aims to evaluate the effectiveness and underlying mechanisms of mobile health (mHealth) platform-supported lifestyle-integrated multicomponent exercise (*PF-Life*) to reverse pre-frailty in community-dwelling older adults.

**Methods:**

This is an open-label, prospective, two-arm parallel randomized controlled trial with allocation concealment and outcome assessment blinding. We aim to recruit 140 pre-frail community-dwelling older adults who will be randomized into two groups. The control group will receive a health education program, while the intervention group will receive *PF-Life* training as planned for 1 year. The proportion of pre-frailty, functional performance (muscular strength, aerobic capacity, flexibility, and balance), body composition, and physical activity will be measured at pre-intervention, post-intervention, and 12-month follow-up. Inflammatory biomarkers will also be collected to explore the underlying mechanisms.

**Discussion:**

This is the first study to evaluate the effects of a novel digital lifestyle-integrated multicomponent exercise for pre-frail older people. The results of this trial will provide much-needed information on the short-and long-term effects of *PF-Life* based on functional performance and body composition. Meanwhile, inflammatory biomarkers and physical activity levels will be used to elucidate the underlying mechanisms of *PF-Life*. The findings from this trial will provide evidence for the effectiveness of lifestyle multicomponent exercise intervention supported by the mHealth platform that may reverse or even halt the onset of frailty.

**Clinical trial registration:**

https://www.chictr.org.cn/showproj.html?proj=176477, identifier ChiCTR2200063431.

## Background

Population aging and its higher demand for healthcare services have led to an increased sense of urgency to develop practical approaches to promote successful aging and prevent age-related diseases and progressive functional decline (1). Frailty is one of the most problematic manifestations of the aging population (2). It is an age-related clinical syndrome characterized by reduced reserve function of multiple physiologic systems; thus, frail older adults are vulnerable to adverse health outcomes (3, 4). The underlying mechanisms of frailty may have often been associated with inflammation and dysregulated energy metabolism. Chronic inflammation has been strongly linked to physical dysfunction and frailty (5). The measurement of inflammation provides a simple way to track the progression of frailty (6).

It is noteworthy that frailty is a dynamic and progressive process (7). Pre-frailty is an early state of frailty characterized by diminished balance, muscle strength, and mobility (8). Although physical dysfunction is not as severe as frailty, the prevalence of pre-frailty is much higher than that of frailty (46% vs. 12%) (9). Moreover, once frailty is clinically manifested, the descent trajectory of physical function is difficult to reverse, and the transition from pre-frailty to health is much more likely than from frailty to health (23% vs. 3%) (10–12). Therefore, pre-frailty represents an ideal window of opportunity to potentially prevent frailty and reduce healthcare costs. Early and effective interventions to delay or reverse pre-frailty are a public health imperative (7).

Regular exercise is the central axis for preventing pre-frailty (13). Multicomponent exercise (aerobic, resistance, and balance training) is the most effective type of exercise (14, 15). Despite the overwhelming evidence that multicomponent exercise is highly beneficial in improving the functional capacity of the pre-frail population, less than one-third of older people engage in exercise and they tend to stop within 6 months, leaving a clear gap between evidence and action (16, 17). Notably, regular exercise is not an easy task for most pre-frail individuals. There are several barriers to exercise, including poor exercise tolerance, inconvenient transportation, lack of time, skills, and motivation, and limited access to exercise resources and funding (18). Thus, integrating exercise into daily life may be an innovative approach to encourage pre-frail adults to adopt active lifestyles and change exercise behaviors (19, 20). The original Lifestyle-integrated Functional Exercise (LiFE) program — developed by Clemson in 2012 for the older person at risk of falls — has been shown to improve physical function, decrease disability, and promote habit formation (21). Contrary to other traditional home-based exercise programs, the LiFE program has demonstrated high adherence and motivation (22, 23). Incorporating multicomponent exercise into daily life may provide a practical option for pre-frail individuals to exercise whenever and wherever they prefer and address the issues of accessibility and cost. However, these home-based exercise programs also present challenges as they struggle to provide on-site supervision, feedback, and encouragement, all of which are crucial factors in improving long-term adherence and efficacy (24).

Therefore, exploring how technological innovation can support such an exercise program is imperative. Recent advances in digital technology, such as wearable sensors and smartphone applications, provide an opportunity to improve uptake and sustainability of exercise programs (25). For instance, objective physical activity (PA) monitoring using wearable sensors can be useful in developing motivational strategies to enhance daily activity (26). Particularly, mobile health (mHealth) platforms consisting of apps and web portals synchronized with wearable devices appear to be an effective way to enable self-management and remote monitoring of home-based exercise (27, 28). To date, little is known about the potential application of mHealth platforms to lifestyle-integrated multicomponent exercise and their effectiveness to prevent pre-frailty.

We have developed a lifestyle-integrated multicomponent exercise program, namely *PF-Life*, based on the mHealth platform in line with current evidence-based principles. This program offers tailored, progressive, lifestyle-integrated multicomponent exercises that incorporate behavioral change strategies such as timely motivation, feedback, reminders, and monitoring. The current randomized controlled trial (RCT) aims to evaluate the effectiveness and the underlying mechanisms of the *PF-Life* program to reverse pre-frailty in community-dwelling older adults. We hypothesize that *PF-Life* reverses pre-frailty, enhances functional fitness (FF), including endurance, flexibility, muscular strength, and balance, improves body composition (BC), increases daily PA, and modulates levels of inflammatory cytokines in a Chinese pre-frail population throughout a 12-month outcome assessment.

## Methods

### Study design and setting

This is an open-label, prospective, two-arm parallel RCT with balanced randomization (1:1), allocation concealment, and outcome assessment blinding. The study protocol employs the Standard Protocol Items: Recommendations for Interventional Trials (SPIRIT) guideline and the Consolidated Standards of Reporting Trials (CONSORT) statement for clinical trial transparency (29). The trial will be conducted at the Fujian Geriatrics Center, which is the largest geriatrics specialty among general hospitals in Fujian Province, China. Participants will be recruited from the *Fujian Prospective Aging Cohort* according to the screening criteria and randomly allocated to two groups: the *PF-Life* program (intervention) group and the health education (control) group. Data from each participant group will be collected at four different times: screening assessment, post-randomization baseline assessment, 4-month outcome assessment, and 12-month outcome assessment. The flowchart of the study protocol is displayed in Figure 1.

**Figure 1 fig1:**
[figure not shown]
Flowchart of the study protocol.

### Participants and recruitment

We aim to include 140 participants in this 1-year RCT. Recruitment will be carried out through posters, lectures, and flyers at the community health centers where the project team previously conducted the *Fujian Prospective Aging Cohort* Study. The cohort study was conducted in five community centers in Fuzhou, China, with a prevalence of pre-frailty of 44% (30). Participants inclusion criteria are: (1) aged ≥60 years; (2) living in the community; (3) fulfilling one or two of the Fried frailty phenotypes (31); (4) a smartphone user; (5) being able to walk independently without an assistive device; and (6) having normal language expression and comprehension (speaking Mandarin). Exclusion criteria are: (1) acute myocardial infarction within the past 3 months; (2) unstable or persistent cardiovascular or respiratory condition; (3) moderate to severe cognitive impairment, psychiatric disorders that prevent cooperation; (4) traumatic fracture (within 6 months); (5) performing moderate-to-vigorous PA more than 150 min per week during the past 3 months; and (6) inability to exercise or other conditions that may interfere with exercise.

### Sample size

The sample size is calculated using the statistical software PASS v11.0 (NCSS, Kaysville, UT, United States). Based on previous studies (32, 33), the proportion of reversing a pre-frailty state in the health education group and exercise groups is assumed to be 10 and 40%, respectively. Using a two-sided Fisher’s exact test and considering a dropout of approximately 20% (34, 35), the trial requires 118 participants (59 in each group, 50% each) to obtain 90% certainty (power = 1-*β*) of detecting a statistical difference at *α* = 0.05 (two-sided) level of significance. In order to increase the efficacy of the study, a total of 140 individuals will be recruited in this study (70 in each group).

### Randomization, blinding, and allocation concealment

To ensure allocation concealment, participants will be randomly assigned to the *PF-Life* group or control group in a 1:1 ratio by study staff (who will not be involved in participant recruitment or outcome assessment). The random number sequence will be generated by the investigator using a simple randomization procedure.^1^ These random numbers will then be individually placed in sequentially coded, sealed, opaque envelopes. The researcher will open the envelopes sequentially and assign random numbers to participants to identify their group. In addition, participants and interventionists will be instructed not to disclose the allocation to outcome assessors and data analysts. Unblinding will occur after all data analyses have been completed and will be carried out by staff not directly involved in the study.

### Intervention group

The exercise program will be delivered using the *PF-Life* mHealth platform, which is designed based on evidence from app developers, designers, geriatricians, and researchers to create personalized digital exercise programs. The mHealth platform consists of a smartphone app synchronized with a wearable device and a web-based portal that provides intensive interactions combined with multiple features and content. Based on Behavior Change Wheel (BCW) framework (36), 12 behavior change strategies, including goal setting, action plans, feedback, and motivation, will be applied in the development of *PF-Life* platform to support a lifestyle integrated exercise (37). The integration of these strategies with the *PF-Life* platform and interventions is described in Supplementary Table S1.

#### Introductory session

The first face-to-face introductory session will be held at the Fujian Geriatrics Center to introduce the *PF-Life* program, customize an exercise program based on functional performance assessment, discuss strategies and techniques for incorporating multicomponent exercise into daily lives, and guide users on how to place the wearable devices and download and use the app.

#### Exercise program

The exercise program is based on and expands upon the standardized LiFE program (21, 38). It is a multi-component exercise program that incorporates four basic functional areas: aerobic conditioning, muscle strengthening, flexibility, and balance training. When designing content, each exercise was specifically chosen to be relevant to daily living activities in the home environment and was easy to incorporate or mimic daily life, such as lifting the toes and heels, chair rise, back scratch, simulated towel wringing, farmer’s walk, etc.

There are 16 sets in the three levels of difficulty based on functional performance: elementary, intermediate, and advanced with increasing complexity. Personalized exercise programs are customized based on the assessment of the participant’s current level of FF in endurance, balance, flexibility, and strength. The exercise programs follow the principle of progression, increasing the exercise load by adding more repetitions and longer training times and using ankle weights at higher levels. For example, the first month of strength training begins with 3 reps per set for 3 sets at 30% one repetition maximum (1RM) loading and progresses in the second month with a gradual progression to 5 reps per set for 3 sets at 80% 1RM. Frequency, Intensity, Timing, and Type (FITT) are based on the FITT Guidelines for Older Adults (39). Participants are advised to train five times a week at their preferred time for 16 weeks. After 16 weeks, participants may continue to use the program for as long as they choose. In addition to the multicomponent exercises, participants are encouraged to increase daily PA and decrease sedentary time through visual charts showing daily PA progress. The exercise program was developed by the research team in consultation with experts in geriatrics, sports medicine, and rehabilitation medicine. The instructional videos were filmed in advance and embedded in the mHealth platform.

#### Implementation of the technology

Participants access the exercise program through the *PF-Life app*. The exercise tasks menu on the main interface present participants with a personalized list of exercises for each week. Tapping accesses the exercise task details, and participants perform the exercises while watching videos on the app. After completion of each exercise, feedback on the participant’s performance is captured on their smartphone and sent to healthcare professionals. Participants access visualized PA data uploaded by the wearable device, ActiGraph wGT3X-BT, as well as task completion, task progress bar, and exercise ranking, for self-monitoring. At the same time, participants use the app to communicate and interact with healthcare professionals via text, voice or video.

The *PF-Life* web portal is designed for healthcare professionals. Healthcare professionals customize exercise programs for each participant through the exercise task features and exercise parameters, and other data are transferred directly to the participant’s smartphone. The web portal allows healthcare professionals to view data from participants’ wearable devices and smartphones, monitor participants’ exercise progress, and make timely adjustments. In addition, healthcare professionals are reminded to intervene when exercise tasks are not completed by sending reminders or motivational text messages. Exercise completion is automatically recorded by the *PF-Life* app during intervention and follow-up, and PA data are uploaded from the wearable device (ActiGraph wGT3X-BT) and synchronized with the *PF-Life* web portal. Healthcare professionals assess and record participants’ adherence to the exercise program by monitoring their physical activity data (the number of days exercised per week, number of sets exercised per day, and the duration of exercised per set). Figure 2 shows screenshots of the main application features and representative functions of the *PF-Life* Platform.

**Figure 2 fig2:**
[figure not shown]
Screenshots of the representative function and wearable device: **(A)** personalized list of exercises for each week, **(B)** visualized physical activity data, **(C)** communication and interaction, **(D)** exercise video, **(E)** exercise monitor, **(F)** customize exercise program, and **(G)** ActiGraph wGT3X-BT.

### Waitlist control group

The control group will maintain their regular lifestyle and daily routine activities. They will also receive four health education sessions once a month, delivered by geriatric specialist nurses in person or via WeChat, including the benefits of exercise for frailty. If the intervention proves effective for the intervention group, the control group will be invited to participate at the end of the study.

### Outcome measures

Table 1 provides a detailed summary of primary and secondary outcome measures for each assessment time point. Data collectors will be blinded to group assignments.

**Table 1 tab1:** Overview of primary and secondary outcomes, outcome measures, and assessment time points.

Outcomes	Outcome measures	Screening	Baseline	16 weeks	1-years
Eligibility assessment	Inclusion criteria	√			
	Exclusion criteria	√			
Primary outcomes					
Pre-frailty assessment	Fried frailty phenotype	√	√	√	√
Secondary outcomes					
Body composition	Body mass index, body fat mass, body fat percentage, fat-free body mass, fat-free mass percentage, and visceral fat level	√	√	√	√
Bone mineral density	Bone mineral density	√	√	√	√
Functional performance assessment	30-s chair rise test	√	√	√	√
	30-s arm curl test	√	√	√	√
	Hand grip strength	√	√	√	√
	Chair sit and reach test	√	√	√	√
	Back scratch test		√	√	√
	Timed up and go test		√	√	√
	Single-leg stance test		√	√	√
	4-m gait speed test		√	√	√
	2-min step test		√	√	√
Physical activity level assessment	Sedentary time (min/d), energy expenditure (MET/h), LPA (min/d), MVPA (min/d)		√	√	√
Inflammatory cytokines	Chemokines (CXCL8/IL-8, CCL5/RANTES, CXCL9/MIG, CCL2/MCP-1, CCL11/Eotaxin and CXCL10/IP-10, CCL4/MIP-1β, CCL7/MCP-3, CXCL1/GROα, CCL3/MIP-1α, CCL28/CTACK, and CXCL11/SDF-α)		√	√	√
	Cytokines (IL-2, IL-3, IL-4, IL-5, IL-6, IL-7, IL-9, IL-10, IL-12, IL-13, IL-15, IL-16, IL-17A, IL-18, IL-1β, TNF-a, TNF-β, IFNγ, and IFNα)		√	√	√
Exploitative outcome assessment	Medical and demographical data	√	√	√	√
	Sustainability		√	√	√

√, data will be obtained; MET, metabolic equivalents of task; LPA, low physical activity; MVPA, moderate-to-vigorous physical activity.

### Primary outcome assessment

The primary outcome is the proportion of participants with pre-frailty in the intervention group compared with the control group over 12 months from baseline, as measured by the Fried frailty phenotype, which is currently an internationally recognized standard for frailty identification and assessment. The frailty criteria have five components (29): (i) unintentional weight loss (>4.5 kg or at least 5% of body mass in the previous year through a self-reported questionnaire); (ii) low handgrip strength (HGS, cutoff points: ≤30 kg for males and ≤18 kg for females); (iii) fatigue [self-reported using questions 7 and 20 of the Centre for Epidemiological Studies Depression Scale (CES-D)]. Study participants are asked how often in the past week they think they have had difficulty completing daily tasks and how often they have been unable to complete activities. A positive response of ‘most of the time’ or ‘always’ to either question is considered an indication of fatigue; (iv) slow gait (≥0.65 m/s walking speed over a 4.5 m distance); and (v) low PA levels (<383 kcal/week for males and <270 kcal/week for females). The presence of one or two of the five components is recognized as pre-frailty.

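### The primary outcome counts participants in the pre-frail state, so becoming frail and recovering both remove a participant from it, while the hypothesis and sample size concern reversal

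*Protocol article*

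**What the plan says.** Under Primary outcome assessment, the protocol article states: "The primary outcome is the proportion of participants with pre-frailty in the intervention group compared with the control group over 12 months from baseline". The same section defines the state: "The presence of one or two of the five components is recognized as pre-frailty". Under Participants and recruitment, entry requires "fulfilling one or two of the Fried frailty phenotypes", so every participant starts in the counted state.

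The Sample size section uses a different quantity: "the proportion of reversing a pre-frailty state in the health education group and exercise groups is assumed to be 10 and 40%, respectively". The hypothesis at the end of the Background is likewise that the program reverses pre-frailty. The Methods paragraph of the abstract and the Statistical analysis section both name the proportion of pre-frailty, as the primary outcome section does.

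Table 1 schedules the Fried phenotype at screening, baseline, 16 weeks and 1 year. Progression to frailty is not among the listed secondary outcomes, and the article does not say how a participant who becomes frail is counted in the primary outcome.

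**The concern.** After enrollment a participant can be robust (0 components), pre-frail (1–2) or frail (3–5). The worded outcome is the share in the middle state. A fall in that share mixes the result the trial hopes for with its opposite.

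Two things follow if the wording is applied literally:

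- **The contrast can be distorted in either direction.** If fewer participants become frail in the intervention arm than in the control arm, that advantage is subtracted from the measured effect. If more do, the excess is counted towards the program.
- **The stated power belongs to another endpoint.** The calculation is for reversal, and it carries over to the proportion with pre-frailty only when nobody in either arm progresses.

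**Working it through.** **Inputs from the protocol article**

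- Reversal: 10% control, 40% intervention (Sample size).
- Test and level: "Using a two-sided Fisher’s exact test", at the "0.05 (two-sided) level of significance".
- Target power: "to obtain 90% certainty".
- Dropout about 20%; 59 per group required, 70 per group planned.

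**Input not in the article:** the proportion becoming frail in each arm. The values below are assumptions.

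**Step 1. Reproduce the plan's figure.** Exact power is the sum of the binomial probabilities of all pairs of counts for which the two-sided Fisher p-value is at most 0.05. For 0.10 v 0.40:

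- 46 per arm: 89.8%
- 47 per arm: 90.6%

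So 47 evaluable per arm are needed. 47 / 0.8 = 58.75, which rounds up to 59 per arm, 118 in total. This matches the article, so the arithmetic is sound for reversal. With 70 per arm and 20% dropout, 70 × 0.8 = 56 are evaluable per arm, and power is 95.3%.

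**Step 2. Express the worded outcome.** In each arm,

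proportion pre-frail = 1 − reversal − progression.

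The between-arm difference (control minus intervention) is therefore

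(reversal, intervention − reversal, control) − (progression, control − progression, intervention).

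With no progression it is 90% − 60% = 30 points, the same as for reversal. Otherwise any gap in progression is subtracted from the 30 points or added to them.

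**Step 3. Power for the worded outcome**, with reversal held at 10% v 40% and 56 evaluable per arm:

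| Assumed progression, control / intervention | Pre-frail, control v intervention | Difference (points) | Fisher power |
|---|---|---|---|
| 0% / 0% | 90% v 60% | 30 | 95.3% |
| 5% / 5% | 85% v 55% | 30 | 92.3% |
| 10% / 10% | 80% v 50% | 30 | 89.8% |
| 12% / 12% | 78% v 48% | 30 | 88.8% |
| 3% / 1% | 87% v 59% | 28 | 90.1% |
| 5% / 2% | 85% v 58% | 27 | 86.3% |
| 10% / 5% | 80% v 55% | 25 | 76.8% |
| 12% / 4% | 78% v 56% | 22 | 64.2% |
| 15% / 5% | 75% v 55% | 20 | 53.8% |
| 20% / 5% | 70% v 55% | 15 | 30.6% |

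As a limiting case, progression of 30% in control and 0% in intervention leaves 60% pre-frail in both arms, so the measured difference is zero despite a 30-point gain in reversal.

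**Step 4. The opposite direction.** Suppose reversal is 10% in both arms, so there is no benefit, and more intervention participants become frail. With progression of 4% control v 12% intervention, the proportions not pre-frail are 14% v 22%, and the chance of a significant result at 56 per arm is 13%. With 5% v 20% (15% v 30% not pre-frail) it is 39%.

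**The case against.** The title, the aim, the hypothesis and the sample size all speak of reversal, so the outcome wording may be shorthand for not yet reversed. A journal article condenses a fuller protocol, and the coding of frail participants may be settled there or in an analysis plan that is not shown. This limits what can be claimed about intent. It does not remove the inconsistency: the same quantity is named in the abstract, the outcome definition and the analysis section, and the definition given there puts frail participants outside the count.

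The power figures depend on progression rates that the article does not give. If progression is equal in the two arms, or nearly so, the loss is modest: 5% v 5% leaves 92%, and 3% v 1% leaves 90%. This stands. The large losses need clearly more progression among controls.

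A reader might infer that a program which caused frailty would simply look effective. That is too strong. Only progression in excess of the control arm's counts towards it, and with no reversal benefit the chance of a significant result is 13% or 39% in the two cases worked above.

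A reader might also take prevention of frailty to be a stated trial objective, so that the outcome contradicts the aim outright. In the article it is rationale and expected implication; the stated aim is to reverse pre-frailty.

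Finally, Fried status is collected at each visit, so reversal can be derived whatever the wording. That makes the repair easy. It does not settle which quantity is primary.

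**Conclusion.** The point holds. As worded, the primary outcome does not separate recovery from worsening, and it is not the quantity that was hypothesised and sized. This follows from the article's own definitions and needs no assumed rate.

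The sample size calculation is correct for reversal. Its 90% power does not automatically carry over to the worded outcome, but no particular loss is established. Over the progression rates tried, power at 56 evaluable per arm ranges from about 92% to 31%, against 95% with no progression, all with reversal fixed at 10% v 40%. Where the trial would fall in that range depends mainly on how far progression differs between the arms, which the documents do not say.

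The sample size text does not fully fix the reversal endpoint either. It refers to "the proportion of reversing a pre-frailty state in the health education group and exercise groups" without naming zero components or a visit, so a reader should not infer that it already assumes zero components at 12 months.

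**What to change.** - Define the primary endpoint as reversal: zero of five Fried components at one named visit, yes or no, with pre-frail and frail both counted as not reversed. The 12-month visit fits the period given in the primary outcome section.
- Add progression to frail (three or more components) as a secondary outcome, and report robust, pre-frail and frail by arm.
- Align the abstract and the Statistical analysis section with this definition, and the trial registration if it uses the same wording.
- Confirm that the 10% and 40% taken from earlier studies refer to this definition and visit. If they do, 59 per arm stands unchanged and 70 per arm gives 95% power after 20% dropout. If they do not, restate the assumption and recheck the size.

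The cost is a few sentences and a check of the sources behind the two rates. No new data are needed, because Table 1 already schedules the Fried phenotype at 16 weeks and 1 year. The change should be made before outcome data are examined, so that the choice between not pre-frail and robust cannot depend on the results.
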